### Data analysis

General descriptive statistics will be performed on baseline patient and fracture characteristics. Patients will be analyzed according to the intention-to-treat principle.

#### Primary outcome

The primary outcome, fracture re-displacement, will be analyzed using a mixed-effects logistic regression. To account for clustering, a random intercept for the hospitals will be used. Fixed effects will be the covariates we adjust for as reported in the literature, namely age, presence of osteoporosis, and fracture characteristics. If new prognostic factors will be identified and reported in the literature, these factors will also be added as covariates.

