### Design, participants, interventions and outcomes

#### Study design and randomization

For this study, a multicenter cluster randomized design is used. All participating hospitals are located in the Netherlands and include the following 10 centres; Alrijne hospital (Leiderdorp), Elisabeth-Tweesteden hospital (Tilburg), Erasmus MC University Medical Center (Rotterdam), Franciscus hospital, location Gasthuis and Vlietland (Rotterdam and Schiedam), Haga Teaching hospital (Den Haag), Haaglanden Medical Center (Den Haag), IJsselland hospital (Capelle aan den IJssel), Maasstad hospital (Rotterdam), Reinier de Graaf Gasthuis (Delft) and St. Antonius Hospital (Utrecht and Nieuwegein).

Two types of cast immobilization will be compared in this trial. Randomization at patient level will be challenging because of the 24/7 availability of the Emergency Department (ED), leading to a high number of treating physicians. To overcome the potential of many protocol violations, we chose to randomise on hospital-level with a cross-over point halfway the needed inclusions per hospital (i.e. after 31 inclusions). This means all patients in one hospital will receive the same intervention, which will change after half of the number of patients are included. This cross-over design is used to overcome potential non-eligibility of both groups because patient populations can differ amongst hospitals. Secondly, possible bias due to existing experience with one of the techniques in each hospital will be diminished. Before the start of the study, an independent researcher not involved in the study, randomly allocated the starting treatments amongst the participating hospitals.

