#### Sample size

The sample size calculation is based on the results of our recent retrospective study [14]. We hypothesize that fracture redisplacement occurs in 10% of circumferential casted patients versus 20% in splinted patients. A total of 500 patients is needed to detect superiority of a circumferential cast. The sample size calculation is based on a mixed-effects logistic regression, to account for clustering using a random intercept for the hospitals. The intra-class correlation coefficient between the different hospitals for the proportion of fracture redisplacement is assumed to be 0.06, which is generally reported in the literature for hospital processes. From the expected proportions of redisplacement in the two groups, we calculated the hospital-specific log odds of secondary displacement in the circular cast group, equal to − 2.275 and log odds ratio of redisplacement between the two groups equal to 0.84. This calculation is based on the formula that links the cluster-specific coefficients in the mixed-effects logistic regression with the population coefficients averaged over the hospitals. With a power of 93%, 50 patients per hospital need to be included, resulting in a total number needed of 500 (10 participating hospitals). Additionally, we also calculated the needed number of patients using a two-sample test for proportions. Using the same assumptions, namely difference between groups, a significance level of 0.05 and a power of 90%. This resulted in 490 needed patients in total. Accounting for a 10% loss to follow-up, a total of 560 (280 patients per group) are required.

To improve awareness of the study in all participating centers and thereby advert for reaching targeted sample size, a local investigator is appointed in each hospital. This local investigator is a physician who supervises the study. This person is easily accessible and will promote the study on a regular base. We send a newsletter every 2 months to inform about the study progression.

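### The primary model and the sample size use only a hospital random intercept although the design is a two-period cluster cross-over; if outcomes vary between periods within hospitals, the test is anti-conservative, moderately so under the plan's own ICC

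*Protocol article*

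**What the plan says.** Under Study design and randomization, the protocol article describes a cluster cross-over with one switch per hospital: "all patients in one hospital will receive the same intervention, which will change after half of the number of patients are included". The switch comes after 31 inclusions. Before the start, an independent researcher "randomly allocated the starting treatments amongst the participating hospitals"; whether this gave five hospitals per sequence is not stated.

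Under Data analysis, Primary outcome: "The primary outcome, fracture re-displacement, will be analyzed using a mixed-effects logistic regression". The random part is given in one sentence: "To account for clustering, a random intercept for the hospitals will be used". The fixed part is: "Fixed effects will be the covariates we adjust for as reported in the literature, namely age, presence of osteoporosis, and fracture characteristics". Neither a period term nor a hospital-by-period term appears.

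Under Sample size, the calculation uses a mixed-effects logistic regression "to account for clustering using a random intercept for the hospitals", with a single ICC of 0.06 and the hypothesis that "fracture redisplacement occurs in 10% of circumferential casted patients versus 20% in splinted patients". It reports a hospital-specific log odds of −2.275, a log odds ratio of 0.84, and 93% power with 50 patients in each of 10 hospitals.

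**The concern.** A hospital random intercept alone suits a trial that randomises patients within hospitals. Here the treatment effect is estimated by comparing one half of a hospital's patients with the other half. The intercept removes whatever is stable in a hospital. It does not absorb what changes between the halves, and the stated model sets that variance to exactly zero.

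The article gives reasons to doubt zero. Inclusion is expected to take 18 months. The switch is triggered by a patient count, so hospitals may switch at different calendar times. Casts are applied by several kinds of staff, and training is tailored to each hospital because experience differs (Interventions). A cast effect that differs between hospitals would also look like hospital-by-period variation in this design, because each hospital gives each treatment in one period only.

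The confirmatory test is at stake. If the variance is not zero, the standard error is too small, and ordinary variation between periods in a few hospitals can pass for a cast effect. The sponsor intends the result to inform the Dutch guideline.

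**Working it through.** **Inputs from the protocol.** 10 hospitals, 2 periods each; 50 patients per hospital in the power calculation, so m = 25 per hospital-period; event rates 10% and 20%; ICC 0.06; significance level 0.05, sidedness not stated.

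**Assumed.** CAC, the ratio of the between-period to the within-period correlation in a hospital, at 1.0, 0.9, 0.8 and 0.5.

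**1. The plan's own figures, and the scale of its ICC.** On the latent logistic scale the hospital variance is σ² = (0.06/0.94) × π²/3 = 0.210. The marginal-to-conditional factor is √(1 + c²σ²) with c = 16√3/(15π) = 0.588, which gives √(1 + 0.346 × 0.210) = 1.0357.
- Cast group: logit(0.10) × 1.0357 = −2.197 × 1.0357 = −2.276 (stated −2.275).
- Log odds ratio: (−1.386 + 2.197) × 1.0357 = 0.840 (stated 0.84).

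So the plan uses 0.06 on the latent scale. On the proportion scale this is roughly p(1−p)σ²: 0.09 × 0.210 = 0.019 at 10% and 0.16 × 0.210 = 0.034 at 20%, or about 0.02–0.03.

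Simulated power for 10 × 50 patients with a hospital intercept only and CAC 1 is 93.9% one-sided and 88.7% two-sided. The stated 93% therefore matches a one-sided 5% test.

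**2. Closed form.** Relative to individual randomisation, the variance of the within-hospital contrast is multiplied by 1 + (m−1)ρ − mρ·CAC. A model that assumes CAC = 1 implies about 1 − ρ. The actual size is then about 2[1 − Φ(1.96/√ratio)], with the ratio of the two.

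Example with ρ = 0.03 and CAC 0.8: 1 + 24 × 0.03 − 25 × 0.03 × 0.8 = 1.12; 1.12/0.97 = 1.155; size 6.8%.

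**3. Simulation.** 4,000 runs per scenario; Monte Carlo standard error about 0.35 points; no treatment effect; event rate about 15%; latent ICC 0.06; 5:5 sequences; no covariates; two-sided 5% Wald test except in the last column.

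| CAC | Closed form, ρ 0.02 to 0.03 | Planned model | + fixed period | + period and hospital-by-period, z | Same, t on 8 df |
|---|---|---|---|---|---|
| 1.0 | 5.0% | 4.8% | 4.8% | 4.3% | 1.5% |
| 0.9 | 5.6–5.9% | 5.7% | 5.7% | 5.0% | 2.1% |
| 0.8 | 6.2–6.8% | 6.4% | 6.5% | 5.5% | 2.5% |
| 0.5 | 8.0–9.6% | 8.8% | 9.0% | 7.0% | 3.0% |

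The closed form brackets the simulation at CAC below 1. With 28 per hospital-period (560/20), a separate simulation of the planned model gave 5.6%, 5.7% and 9.2% at CAC 0.9, 0.8 and 0.5. With a latent ICC of 0.02 and CAC 0.8, the size is 5.2%.

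**4. Upper scenario.** With 0.06 on the proportion scale and m = 25, CAC 0.8 gives 1 + 1.44 − 1.20 = 1.24; 1.24/0.94 = 1.319; size 8.8%. CAC 0.9 and 0.5 give 6.9% and 14.4%. Simulation with m = 28 gave 7.0%, 8.9% and 15.0% at 0.9, 0.8 and 0.5.

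**5. Common period effect alone.** With CAC 1 and a period log odds ratio of 0.5, the planned model has size 5.2% with 5:5 sequences and 6.8% with 6:4. A fixed period term gives 4.9% and 5.1%.

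**6. Two-sided power at 500 patients.** With the hospital-by-period term and Wald z: 85.8%, 85.5% and 82.5% at CAC 0.9, 0.8 and 0.5. With t on 8 df: 76.8%, 76.3% and 73.3%.

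**The case against.** The strongest reply is that nothing in the protocol shows hospital-by-period variation to exist. If there is none, the planned test is at its nominal level (4.8%). At CAC 0.8–0.9 the excess is within about 1.5 points. This stands: a reader might infer that the type I error simply exceeds 5%, and the document does not support that without an assumed CAC.

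A reader might also take the ICC wording, which speaks of the proportion of redisplacement, at face value and arrive at 7–15%. The protocol's −2.275 and 0.84 reproduce on the latent scale, so that range is an upper scenario only.

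Nor does the missing period term do the damage alone. Adding it left the inflation unchanged, and omitting it was harmless with 5:5 sequences. It matters only if sequences or period sizes are unbalanced. Balance is not stated, but neither is imbalance, and the allocation method may be in the full protocol. A first/second-period term would also not track season when the switch is triggered by a count.

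Finally, the article is condensed. Its fixed-effects list omits even treatment, so it cannot show that period was ruled out, and it does not say that Wald inference will be used. Small-sample methods are ordinary analysis-plan content, so their absence is no fault. What the reply does not remove is the random structure, which is stated in the analysis section and again in the sample size, and which does not match the design.

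**Conclusion.** The point holds conditionally. The stated primary model and sample size leave out hospital-by-period variation in a design where treatment is compared between periods. If that variance is not zero, the standard error is too small. Under the plan's own ICC the two-sided 5% test then runs at about 6–9% for CAC from 0.9 to 0.5. This rests on the latent-scale reading of 0.06, 25 patients per hospital-period, balanced sequences, a Wald test, no covariates, and CAC values that the document does not give. It is a moderate inflation of the confirmatory test, and it does not show that a positive result would be false.

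The gap between the stated 93% power and 82–86% has two parts. Moving from a one-sided to a two-sided test takes 93.9% to 88.7%; the hospital-by-period term takes it to 85.8–82.5%.

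**What to change.** Specify the primary model with treatment and period (first or second) as fixed effects, the planned covariates, a random hospital intercept and a random hospital-by-period intercept. Prespecify the small-sample method and check it by simulation for 10 hospitals, because the obvious choices err in both directions: Wald z still gave 7.0% at CAC 0.5, and t on 8 df was conservative at 1.5–3.0%. One candidate is a period-adjusted analysis of hospital-period summaries on 8 df, which held 4.7–5.4% in simulation with 28 patients per hospital-period. Its power was not worked out here and should be part of the check.

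Restate the power under the chosen model, giving the assumed within-period and between-period correlations and the sidedness of the test. State whether the starting sequences were balanced.

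The cost is analysis wording and a short simulation, with no change to conduct. The downside is a wider confidence interval and lower stated power: about 82–86% two-sided at 500 patients with Wald z, and 73–77% with t on 8 df. The change should be fixed before outcome data are examined; made afterwards, it could look driven by the result.

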## Background

Displaced distal radius fractures (DRF’s) are very common in the adult population and their incidence is still increasing because of the ageing population [1, 2]. In the Netherlands, the incidence of DRFs is estimated at 20 per 10.000 persons per year [3]. Two-thirds of DRFs in adults are displaced and require closed reduction [4]. After successful reduction, DRFs are generally immobilized using a non-circular splint or a circumferential cast. Unfortunately, a large number of reduced DRF’s (32–64%) redisplace during cast immobilization in the first treatment weeks [5–7]. Whereas redisplacement of DRFs was previously accepted or reduced in a second attempt, nowadays these redisplaced fractures are generally treated surgically [8, 9].

Although surgical reduction and fixation generally results in a satisfying outcome, preventing fracture redisplacement and thereby preventing surgery would be the preferred scenario. Therefore, it is important to discover factors that could predict or prevent fracture redisplacement. Studies focusing on this topic are mostly assessing non-modifiable factors predicting fracture redisplacement [5–7, 10]. Known factors enhancing the risk on fracture displacement are female gender, age > 60 years and fractures with dorsal comminution [10]. However, it is unknown if type of cast immobilization is of influence.

Existing literature concerning the role of cast immobilization on fracture re-displacement is scarce and inconclusive [11]. Recently, Caruso et al. (2019) performed a randomized controlled trial comparing the effect of above-elbow casting and below-elbow casting on maintaining reduction and found similar results in both groups [12]. Patient-reported outcome after 1-year follow-up did not differ amongst both treatment groups. A randomized controlled trial by Wik et al. (2009) evaluated fracture alignment during 5 weeks follow-up in 72 patients with displaced DRF’s treated with dorsal splinting versus circumferential casting [13]. The circumferential casting group showed a significantly better result for radial length at 5 weeks but no difference concerning dorsal angulation. Recently, our research group conducted a retrospective study in 500 patients with reduced DRFs and found significantly less fracture redisplacement in fractures treated with circumferential casting compared with splinting, namely 17% versus 29% [14].

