#### Study procedures and timeline

Measurements will take place at 7 time points as shown in Table 1. These time points are: baseline (T0), 1 week (T1), 2 weeks (T2), 5 weeks (T3), 3 months (T4), 6 months (T5) and 1 year (T6) after inclusion in the study. At T0, baseline characteristics will be gathered. An inclusion form will be filled in by the treating physician providing fracture and treatment-specific information. Second, patients receive a questionnaire, providing predominantly patient and injury-specific information. The list of baseline characteristics is shown in Table 2. Patients receive questionnaires at T1 to T6. These questionnaires are carried out by email with the use of data capture system GemsTracker [19]. GemsTracker (GEneric Medical Survey Tracker) is a secure web-based application for distribution of questionnaires and forms during clinical research and quality registrations. Receiving questionnaires on paper is optional, as well as telephone interviews. Reminders will be automatically sent. When the patient does not respond to emails, we will contact the patient by telephone. Posterior-anterior (PA) and lateral radiographs of the wrist will be taken at T0 (before and after reduction) and during follow-up at T1 –T3. Physical examination of the wrist will take place at T4 and will be performed by the researcher. If patients are not able to visit the hospital, a home visit will be offered to improve the follow-up.

**Table 1 Tab1:** Overview of measurements

	T0	T1	T2	T3	T4	T5	T6
	Baseline	1 week	2 weeks	5 weeks	3 months	6 months	1 year
Inclusion form	x						
X-rays^a^	x	x	x	x			
Function tests ^b^					x		
*NRS*		x	x	x	x	x	x
*Comfort of cast*		x	x				
*Analgesic use*		x	x	x	x	x	x
*EQ 5D5L*		x^c^		x	x	x	x
*QDASH*				x	x	x	x
*PRWHE*				x	x	x	x
*MCQ-iMTA*				x	x	x	x
*PCQ-iMTA*				x	x	x	x

^a^ X-rays before and one after reduction

^b^ Concerning ROM, grip strength and specific tests

^c^ EQ 5D5L status pre-fracture and post-fracture sustainment

Questionnaires are written in *italics*

**Table 2 Tab2:** Baseline characteristics

Inclusion form	Questionnaire
Date of emergency room visit	Sex
Affected wrist	Date of birth
Method of reduction	Length
Reduction executed by: *(*e.g. *specialist, resident, intern, nurse, cast technician)*	Weight
	Hand dominance
Number of reduction attempts	Mechanism of injury
Type of cast applied	Smoking status

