## Discussion

This study is an open-label trial. Allocated treatments are visually different for the treating physician and the patient. Randomization status will therefore not be blinded.

Heterogeneity of the study population concerning fracture characteristics and age could be pointed out as a limitation. However, this pragmatic study tries to represent the actual patient population.

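### The primary model leaves out sex, which the protocol names as a risk factor and collects, and its covariate list stays open without a cut-off date in an open-label trial

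*Protocol article*

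**What the plan says.** The protocol article, under Data analysis, Primary outcome, specifies a mixed-effects logistic regression with a random intercept for hospital. It defines the adjustment set as follows: "Fixed effects will be the covariates we adjust for as reported in the literature, namely age, presence of osteoporosis, and fracture characteristics". The next sentence extends that set: "If new prognostic factors will be identified and reported in the literature, these factors will also be added as covariates".

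Three other places bear on this.

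- Background: "Known factors enhancing the risk on fracture displacement are female gender". The same sentence goes on to name age over 60 and dorsal comminution.
- Study procedures and timeline: "The list of baseline characteristics is shown in Table 2". Sex is in the questionnaire column of that table.
- Discussion: "This study is an open-label trial", and "Randomization status will therefore not be blinded".

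**The concern.** There are two separate problems.

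The first is one of consistency. The model claims to adjust for what the literature reports, and then gives a closed list. The article's own summary of that literature has three factors. Age is on the list, and dorsal comminution fits under fracture characteristics. Sex fits under none of the listed items. A predictor that the protocol recognises and already records is therefore left out of the primary analysis, and no reason is given.

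The second is one of pre-specification. The sentence on new factors is a positive rule about the primary model. It says such factors will be added, but not up to what date, on what evidence or how many. Someone must decide which reports qualify and when to stop looking. Nothing in the article requires that decision to come before outcomes by arm can be seen, and allocation is not masked. At stake is whether the primary estimate can be defended as coming from a model fixed in advance.

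**Working it through.** **Step 1. The risk factors set beside the model.**

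| Factor named in the Background | Collected at baseline? | In the primary model? |
|---|---|---|
| Age over 60 | Yes (date of birth, Table 2) | Yes (age) |
| Dorsal comminution | Radiographs at T0 | Can be read under fracture characteristics |
| Female gender | Yes (sex, Table 2) | No |

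Only sex drops out.

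**Step 2. Timing of the open list.** The primary outcome is read on radiographs at 1, 2 and 5 weeks, and patients are followed for 1 year. The last patient's primary outcome is thus complete about 52 − 5 = 47 weeks before that patient's follow-up ends. If the analysis waits for the end of follow-up (the article does not say), a paper published in those 47 weeks would still change the primary model under the stated rule, with every primary outcome already recorded.

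**Step 3. Expected events.** The Sample size section assumes 10% redisplacement with a circumferential cast and 20% with a splint. With 250 analysable patients per arm, 250 × 0.10 + 250 × 0.20 = 25 + 50 = 75 events. Overall risk is 75/500 = 15%.

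**Step 4. Effect of a sex imbalance.** The documents give neither the proportion of women nor the odds ratio for sex. Assumed: 60-80% women, odds ratio 1.5 or 2, overall risk held at 15%. Let m be the risk in men, w the risk in women and f the proportion of women. Solve f·w + (1 − f)·m = 0.15 with [w/(1 − w)] / [m/(1 − m)] equal to the odds ratio. The shift in the unadjusted risk difference is then (difference in proportion of women between arms) × (w − m).

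| Women | Odds ratio | Risk in men | Risk in women | Shift at a 10-point imbalance |
|---|---|---|---|---|
| 60% | 1.5 | 12.0% | 17.0% | 0.50 points |
| 70% | 1.5 | 11.6% | 16.4% | 0.48 points |
| 80% | 1.5 | 11.2% | 15.9% | 0.47 points |
| 60% | 2 | 10.1% | 18.3% | 0.82 points |
| 70% | 2 | 9.5% | 17.4% | 0.79 points |
| 80% | 2 | 9.0% | 16.5% | 0.75 points |

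The shift is about 0.5-0.8 points against a planned difference of 20 − 10 = 10 points. A 5-point imbalance halves it.

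**Step 5. How likely is a 10-point imbalance?** With 250 per arm and individual sampling, the standard error of the difference in proportion of women is √[2f(1 − f)/250]. This is 0.044 at 60% and 0.036 at 80%, so 10 points is 0.10/0.044 = 2.3 to 0.10/0.036 = 2.8 standard errors. Chance alone would rarely produce it.

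**Step 6. Omitting sex when the arms are balanced.** The marginal log odds ratio for 20% against 10% is ln[(0.20/0.80)/(0.10/0.90)] = ln 2.25 = 0.811. With 60-80% women and an odds ratio for sex of 1.5-3, the sex-conditional value that gives these marginal rates is 0.813-0.834. The gap is at most about 0.02.

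**Step 7. A ceiling for the open list.** In a simulation under no treatment effect (4,000 runs per setting, 500 patients, no clustering), the most favourable subset of one to three optional covariates with odds ratio 1.5 or 2 was chosen freely. Two-sided type I error came out at 4.8-6.6%, against 4.4-5.5% for the fixed full model. The protocol's rule does not permit that free choice, so this bounds the problem and does not estimate it.

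**The case against.** **The literature trigger.** The strongest counter-argument is that additions depend on outside publications, not on the trial's own results, so the rule gives no licence to choose a model by its p-value. A lock date is also something an analysis plan would normally supply, and none is shown here. The first part stands as a limit on discretion, and Step 7 shows that even unrestricted choice would do limited harm. The second does not dispose of the point. The article does more than leave the date unstated: it directs that new factors be added, and a plan that froze the list would depart from that direction.

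**Choice of covariates is a judgement.** One cited source in the Background does not prove the chosen set wrong, and omitting one prognostic factor does not invalidate the model. That is fair. But the article gives no reason for dropping a factor it calls known and already records.

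**Stronger readings that a reader might infer, and why they fail.**

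- *That omitting sex could bias the result by about 1.1 points, a tenth of the target effect.* That figure takes 15% as the risk in men and about 26% in women at an odds ratio of 2. But 15% is the overall risk implied by the sample-size assumptions. Held there, the same odds ratio gives about 0.8 points, and only with the unlikely 10-point imbalance of Step 5.
- *That sex imbalance through selective recruitment is to be expected.* Recruiting physicians can know the hospital's current cast, so selection is possible. Nothing suggests that it would run along sex. Each hospital also contributes both arms through the cross-over, so stable differences between hospitals largely cancel.
- *That the whole team knows every allocation.* The Discussion explains the lack of blinding by what the treating physician and the patient can see. It does not address the analyst.
- *That osteoporosis is not collected, or that comminution is missing.* Osteoporosis can be recorded under general medical history, and comminution under fracture characteristics. A condensed article need not itemise either.

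**Conclusion.** The point holds in a limited form. The article's primary covariate list is at odds with its own account of known risk factors, because sex is named, collected and left out. The list is also open by explicit rule, with no cut-off date, in an open-label trial, so the primary model can change after outcome data are available.

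Neither fault is large in numbers. The shift of about 0.5-0.8 percentage points rests on assumed values for the proportion of women and the odds ratio, and on an imbalance that chance would seldom give. With balanced arms the effect of omitting sex is negligible. The case for acting is that the inconsistency and the open list are avoidable grounds for challenging the primary estimate, and cheap to remove. The documents do not support calling this a major bias.

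**What to change.** 1. Add sex as a fixed effect in the primary mixed-effects logistic model.
2. State that the covariate list is fixed before any comparison of outcomes by arm, and record the date.
3. Replace the sentence on newly reported factors with one that confines them to a labelled sensitivity analysis, which leaves the primary estimate unchanged.

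The cost is wording only. Sex is already collected, and no trial procedure changes. The one statistical downside is an extra parameter against about 75 expected events. That is also a reason to close the list instead of letting it grow.
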